### Randomization and blinding

The following information will be collected: demographic information, medical history, medication and rehabilitation details, stroke type, time post stroke onset, complications, comorbidity and baseline outcome measures.

We will randomize all the included patients into the three groups at a ratio of 1:1:1 through a computer-generated random number table centrally generated in Tongji Hospital. An independent statistician will prepare the sequentially numbered, opaque, sealed envelopes before the start of enrolment. No randomization number will be reutilized in any case. Because the training methods differ between groups and according to the features of the robot, it is not feasible to blind the subjects, therapists or physicians participating in the trial. Therefore, an independent evaluator at each centre blinded to the randomization procedure and group allocation will assess all outcome measures (baseline, post-intervention and follow-up measures).

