### Sample size

The sample size was calculated by considering the primary outcome measure as the reference: a mean difference of 5 points in the FMA-UE between the AOT-EXO group and CT group and 3 points between the AOT-EXO group and EXO group with a standard deviation of 5.0 [33]. Based on multiple comparisons significance level of 1.67% and a power of 0.8, a sample size of 40 per group will be needed. Assuming that 10% patients loss to follow-up, we will choose a sample size of 44 participants for each group and 132 participants in total. The sample size calculation was performed with PASS 2008 software.

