### Statistical analyses

All statistical analyses will be performed using SPSS software (version 21.0, IBM Corporation, Chicago, IL). To assess the normal distribution of quantitative data, the Shapiro-Wilk test will be employed (*P* > 0.05). Continuous variables will be presented as the mean (SD) for normal distributions and median for non-normal distributions and categorical variables will be presented as frequencies or percentages. Baseline data between groups will be compared using Student’s t-test for continuous variables and the chi-square or Fisher’s exact tests for categorical variables. A *P* value < 0.05 will be considered indicative of statistical significance. All analyses will be carried out based on the intention-to-treat principle, with missing data calculated using multiple imputation. Within-group differences will be assessed using paired t tests for the normally distributed data and Wilcoxon-signed rank test for the non-parametric equivalent test. When comparing the two patient subgroups at each time point, Student’s *t* test (for continuous data) and Fisher’s exact test (for categorical data) will be implemented. When examining the effect of the randomization procedure over time, two-way repeated measures analysis of variance (ANOVA) will be conducted to examine the time-treatment group interaction, with time as the within-group variable and treatment group as the between-group variable.

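### Multiple imputation is paired with a univariate repeated measures ANOVA whose 4-df interaction F does not pool by the ordinary rules and assumes sphericity; with naive pooling, a nominal 5% test runs at roughly 6-10%

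*Protocol article*

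**What the plan says.** Three statements in the protocol article meet here.

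- Missing data (Statistical analyses): "All analyses will be carried out based on the intention-to-treat principle, with missing data calculated using multiple imputation".
- Test over time (Statistical analyses): "two-way repeated measures analysis of variance (ANOVA) will be conducted to examine the time-treatment group interaction". Time is the within-patient factor and treatment group the between-patient factor.
- Threshold (Statistical analyses): a P "value < 0.05 will be considered indicative of statistical significance".

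The Sample size section makes clear that imputation will be needed: "Assuming that 10% patients loss to follow-up", with 44 patients per group. Under Outcomes, FMA-UE is measured at baseline, 4 weeks and 12 weeks, and the primary outcome is its mean change. Under Intervention, trial treatment lasts 4 weeks.

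The article names no sphericity correction and no rule for combining results across imputations. It also does not say that either will be left out. It gives no within-patient correlation or covariance.

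**The concern.** The two named methods sit awkwardly together, for two separate reasons.

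**Pooling.** The ordinary combining rules take an estimate and its standard error from each completed data set and add the between-imputation variance. An omnibus F supplies neither. Each completed data set gives an F that treats imputed values as if they had been observed. Averaging these F or P values, or taking the median P, leaves the uncertainty about the missing scores out of the test.

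**Sphericity.** The univariate F assumes that differences between any two visits have equal variance. With no trial treatment between weeks 4 and 12, those two scores may well lie closer to each other than either does to baseline, and the uncorrected F then rejects too often.

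At stake is the credibility of the time-by-group test: it could declare a difference in recovery too often, and the imputed data sets can disagree on significance.

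**Working it through.** **Inputs from the article.** Three groups, three visits, 44 per group (132 in total), 10% loss to follow-up, threshold 0.05, SD 5.0 for FMA-UE. The article gives no error rate for the interaction test beyond the nominal 5%, so there is no planned figure to reproduce. The sample-size calculation does not bear on this point.

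**Degrees of freedom.** Interaction: (3 − 1)(3 − 1) = 4. Error: (132 − 3)(3 − 1) = 258.

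**Step 1: sphericity alone, complete data.** Suppose change from baseline has equal SD at both later visits, and let r be the correlation of the 4- and 12-week changes (an assumption). The two orthonormal visit contrasts then have variances proportional to λ₁ = 1 − r and λ₂ = (1 + r)/3, and ε = (λ₁ + λ₂)² / [2(λ₁² + λ₂²)].

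- r = 0.5: λ = 0.5 and 0.5, ε = 1.00
- r = 0.7: λ = 0.3 and 0.567, ε = 0.91
- r = 0.8: λ = 0.2 and 0.6, ε = 0.64/0.80 = 0.80
- r = 0.9: λ = 0.1 and 0.633, ε = 0.65

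Rejection rate of the uncorrected F under no treatment effect, 44 per group: 5.0% at ε = 1, 5.6% at 0.9, 6.4% at 0.8, 7.25% at 0.7, 8.2% at 0.6, and 9.4% at the lower bound of 0.5.

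**Step 2: add imputation.** Null simulation with 15,000 trials per row and 44 per group. Dropout at 12 weeks is completely at random, and half of the dropouts also miss week 4. There are 20 normal-model imputations. The covariances are assumptions (SDs at the three visits; correlations baseline-4, baseline-12, 4-12 weeks):

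- ε = 1.00: SDs 10, 10, 10; correlations 0.8, 0.8, 0.8
- ε = 0.76: SDs 10, 12, 13; correlations 0.8, 0.7, 0.9
- ε = 0.60: SDs 10, 13, 14; correlations 0.8, 0.75, 0.97

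Only the pattern matters, because the F does not depend on scale. False-positive rates (%) at nominal 5%; GG is the Greenhouse-Geisser correction:

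| ε | Dropout | Complete data, uncorrected | Complete data, GG | Mean P | Median P | Mean F | Median P with GG | Multi-parameter Wald |
|---|---|---|---|---|---|---|---|---|
| 1.00 | 5% | 5.3 | 5.2 | 5.7 | 6.3 | 6.3 | 6.2 | 5.3 |
| 1.00 | 10% | 5.1 | 5.0 | 6.2 | 7.4 | 7.6 | 7.3 | 5.3 |
| 0.76 | 5% | 6.5 | 5.0 | 7.0 | 7.8 | 7.9 | 5.9 | 5.3 |
| 0.76 | 10% | 6.9 | 5.2 | 7.6 | 9.1 | 9.3 | 7.1 | 5.1 |
| 0.60 | 5% | 8.6 | 5.2 | 8.6 | 9.4 | 9.3 | 5.9 | 5.1 |
| 0.60 | 10% | 8.4 | 5.2 | 8.8 | 10.4 | 10.5 | 6.5 | 5.2 |

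Simulation standard error: √(0.05 × 0.95/15,000) = 0.18 points at 5%, and √(0.10 × 0.90/15,000) = 0.24 points at 10%.

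The last column tests the four interaction contrasts with D = q̄′Ū⁻¹q̄ / [4(1 + ρ)], where ρ = (1 + 1/M) tr(BŪ⁻¹)/4. Here q̄ is the mean contrast vector, Ū the mean within-imputation covariance, B the between-imputation covariance and M the number of imputations. The factor 1 + ρ carries the uncertainty that the naive rules drop.

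**Step 3: other settings.** With SD of change 5, r from 0.5 to 0.9, 10% missing, five imputations and 3,000 trials, the median P gave 7.4-9.9% and a single completed data set 7.9-10.4%. The five imputations disagreed on significance in 10-12% of null trials. Another null simulation at 10% missing gave 7.7-9.6% for the uncorrected median P and 6.5-7.6% with Greenhouse-Geisser.

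**Reading.** With sphericity and 10% dropout, imputation with naive pooling alone moves the rate from 5.1% to 6.2-7.6%. Correcting for sphericity removes only the other component.

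**The case against.** The strongest reply is that the article does not describe the faulty implementation. It nowhere says that F will go uncorrected or that P values will be averaged. A condensed article commonly leaves the pooling rule, the number of imputations and the sphericity correction to the analysis plan, so their absence is no error. This stands, and it makes every figure above conditional.

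A reader might infer three stronger things that the documents do not support.

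- *That the trial has a false-positive rate of 7-10%.* This needs naive pooling, no correction and, in most settings, a departure from sphericity. The article fixes none of them. Across the settings tried, rates run from about 5% to 10.5%.
- *That imputation and this interaction test cannot be combined.* They can: the four contrasts have a covariance matrix, and multi-parameter pooling held 5.1-5.3% throughout.
- *That the primary conclusion rests on this test.* The article does not name the interaction as primary. The trial is sized on pairwise FMA-UE differences, and two-group t tests are planned alongside. Mean differences pool without difficulty, and those t tests may be meant for change scores.

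The reply does not dispose of the point. The article goes beyond leaving details open: it selects two methods that work together only if a less usual pooling rule is added. Adding a sphericity correction, the most familiar repair, would not be enough.

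**Conclusion.** The point holds as a poor choice of paired methods with a conditional consequence. If the interaction F or its P values are pooled naively and left uncorrected, the nominal 5% test runs at roughly 6-10%. With Greenhouse-Geisser and naive pooling it runs at about 6-7.5%. With multi-parameter pooling it is close to 5%. These figures assume 44 per group, 5-10% dropout completely at random, normal scores and within-patient covariances that are not in the documents. The plan should be changed, because a better analysis costs almost nothing. The point does not show that the trial's main comparison is invalid.

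**What to change.** For FMA-UE and the other repeated continuous outcomes, replace the repeated measures ANOVA with a mixed model for repeated measures: fixed effects for group, visit and group-by-visit, unstructured covariance over the three visits, fitted to all observed values with MIXED in the SPSS package already named. Test group-by-visit in this model and take the pairwise group differences in change at 4 and 12 weeks from it. It needs neither imputation nor sphericity. Keep multiple imputation as a sensitivity analysis of the pairwise mean differences, which the scalar rules pool properly.

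If the sponsor prefers imputation for the main analysis, state that the four interaction contrasts will be tested with the multi-parameter Wald pooling rule, and give the number of imputations.

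The mixed model was not simulated here. The nearest evidence is that Wilks' test, which also leaves the covariance unstructured, stayed with Greenhouse-Geisser at 4.7-5.6% on complete data. The cost is a few sentences of analysis text and a different procedure call, with no new patients, visits or data.

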## Discussion

Previous studies have demonstrated that robot-assisted training is effective in promoting upper extremity muscle strength and motor function after stroke [11]. Additionally, action observation treatment can enhance the effects of physical and occupational therapy by increasing neural activation [16]. However, compared with conventional therapy, the results fail to show a superior effect in arm function and ADL. We hypothesize that action observation treatment coupled with robot-assisted training may enhance motor circuit activation and facilitate upper extremity recovery. Therefore, in this study, we aim to evaluate the effects of AOT-EXO for the upper extremity after stroke and to explore the potential mechanisms underlying its effects.

Several features distinguish this study from previous reports. First, to our knowledge, the AOT-EXO trial is the first clinical trial to integrate robot-assisted training with action observation treatment. As mentioned before, robot-assisted training provides highly intensive and task-specific training based on motor learning theory to boost neural plasticity, while AOT specially primes the mirror neural system to activate motor circuits during training. The combination protocol may exert fortifying effects on post-stroke upper extremity rehabilitation. Second, few previous studies have focused on fMRI and corticospinal excitability changes in stroke patients receiving robot-assisted training. The present study is important for further understanding the neural plasticity mechanisms of motor function recovery to enhance the effectiveness of the present therapies. In addition, the AOT-EXO study will provide extensive kinematic assessments evaluating end-point motor performance and movement smoothness reflecting intersegment coordination.

The present study has some limitations. The exoskeleton in this protocol is very large and not MRI-compatible; thus, it is not possible to evaluate the activation of brain regions using fMRI during therapy. The development of MRI-compatible robots or neurofeedback-based training (e.g. functional near-infrared spectroscopy, electroencephalography, and magnetoencephalography) may allow real-time acquisition of the structural, electrophysiological and metabolic changes in the brain to achieve more satisfactory results during robot-assisted training in the future [34]. Moreover, the ADL-related exoskeleton training is still unable to simulate real ADL. Virtual reality may engage patients, increase their attention and improve motivation during robotic training [35]; hence, we plan to incorporate virtual reality technique in the action observation process to match the ADL contents in the next generation of the present exoskeleton.

In conclusion, this study aims to evaluate the effects of AOT-EXO for the upper extremity after stroke and to explore the potential underlying kinematic and neurological mechanisms. The results of the trial will provide evidence regarding the feasibility and effectiveness of AOT-EXO for post- stroke upper extremity rehabilitation.

### Trial status

Current recruitment. At the time of submission, 12 stroke patients have been enrolled.

Protocol version number V1.0, December 2018. Recruitment began on 18 October 2019, and it is anticipated that this trial will be completed by December 2021.

## Data Availability

We aim to publish results derived from this project in international peer-reviewed scientific journals. Data file are available from the corresponding author upon reasonable request.

## Abbreviations

ADL: Activities of daily living
AOT: Action observation therapy
AOT-EXO: Action observation treatment-based exoskeleton
APB: Abductor pollicis brevis
ARAT: Action Research Arm Test
BOLD: Blood oxygen level dependence
CRF: Case report form
DMC: Data monitoring committee
FMA-UE: Fugl-Meyer Assessment of the Upper Extremity
fMRI: Functional magnetic resonance imaging
MBI: Modified Barthel Index
MEP: Motor evoked potentials
MMSE: Mini-Mental State Examination
MNS: Mirror neuron system
RCT: Randomized controlled trial
rMT: Resting motor threshold
TSC: Trial Steering Committee
